#### Standard model of care

Mojo district hospital (Oromia region) has approximately 80 beds and has an established HIV clinic caring for approximately 250 individuals. The hospital is located 179 km from Addis Ababa, and has a catchment population of approximately 70,000 individuals ([name]: Regional database. Oromia Regional Health Bureau, Addis Ababa, Ethiopia, personal communication). The hospital has access to basic laboratory services including biochemistry.

Degehabur hospital (Somali region) is situated in Degehabur town with approximately 48,000 inhabitants [19]. It provides internal medicine, general surgery, paediatrics, gynecology/obstetrics, and has an HIV clinic. This primary hospital has a catchment area of approximately 1,000,000 inhabitants from a vast and scarcely populated area ([name]: Regional database. Somali Regional Health Bureau Jigjiga, Ethiopia, personal communication).

#### Simplified model of care

Batu general hospital (Oromia region) is located in Batu town, in the East Shewa zone, approximately 160 km from Addis Ababa. The town has approximately 80 000 people [19]. The hospital has 60 beds, and has a well-functioning HIV clinic.

Gode general hospital (Somali region) is located in the Shabelle zone, and has a catchment area of approximately 1,500,000 inhabitants ([name]: Regional database. Somali Regional Health Bureau Jigjiga, Ethiopia, personal communication). The main in-patient services at the hospital are medical, surgical, pediatrics, orthopedics, gynecology-obstetrics, dermatology, psychiatry, intensive care, and a malnutrition center. The hospital also runs an HIV clinic.

#### Test-and-treat model of care

Sebata health centre (Oromia region) lies in the south west Shewa zone around 40 km from Addis Ababa. The center employs 40 clinical staff (including one physician), and has an HIV clinic providing care to 1200 patients. The catchment area of the health center is approximately 50,000 individuals ([name]: Regional database. Oromia Regional Health Bureau, Addis Ababa, Ethiopia, personal communication).

Biki general hospital is located in Biki town with approximately 10,000 inhabitants [19]. The town lies 250 km from Jigjiga, the capital of the Somali region, but with limited access due to poor road conditions. The hospital has a catchment population of approximately 300,000 ([name]: Regional database. Somali Regional Health Bureau Jigjiga, Ethiopia, personal communication), and has basic laboratory services such as biochemistry and a well-run HIV clinic.

Each study site will have a team composed of 3-5 individuals responsible for screening, inclusion, delivery of the intervention, and follow-up of participants. This will typically be one medical doctor (or health officer), one nurse, one laboratory technician and one data clerk. Team composition will depend on location, accesibility of personnel, and experience of those identified. The study teams will be identified by the local study site and fully integrated into existing clinical infrastructure at the sites. The study aims to utilize existing staff employed at the local health centers/hospitals.

### Sample size and duration of the study

The sample size has been calculated for the primary outcome (death or liver decompensation) with 80% power and 5% risk of type I error. We anticipate that 5% of all included patients (treated and untreated) will either die or experience liver decompensation within 3 years, with the standard model [20], and we want to detect a 50% relative reduction (Odds Ratio of 0.5 or less) with the test-and-treat model. This results in a sample size of 997 patients per arm [21]. We will increase the sample size by 50% and aim for 1,500 patients per model of care arm, due to expected attrition. This results in a total of 4,500 patients at six different sites. Assuming that approximately 9% of those living in the study setting are hepatitis B surface antigen (HBsAg) positive and 50% of those screened can be included in the study, we estimate that we need to screen approximately 100,000 individuals in order to enroll 4,500 CHB patients.

As inclusion rates may vary across sites, we plan to continue inclusion until all models of care have reached 1500 inclusions, accepting an uneven distribution between the two clinics assigned to the model. We expect to complete inclusion within 1 year. As the observation period will be three years, the total study period will be four years. The first participant was enrolled at September 5, 2024, and recruitment is ongoing. 

### Screening activities

Screening for HBsAg at the various sites will be conducted as determined by the local teams, and will include screening at the hospital premises, at local schools, markets, factories, or religious institutions. Rapid diagnostic tests (RDTs) will be used for screening, based on availablility. A confirmatory test will be done at enrolment in the CHB programme. After initial screening, HBsAg positive individuals will counselled and referred to the HBV clinic for HBsAg confirmation testing using the WHO prequalified Determine HBsAg 2 RDT (Abbott Diagnostics, IL, USA) and enrolment in CHB care. All HIV negative adults>18 years with a positive HBsAg confirmation test are eligible for inclusion. Those who are found to be HIV positive at baseline will be referred to the local HIV treatment unit, and not be enrolled in the present project.

### Recruitment and obtaining informed consent

All eligible individuals will be informed about the study in their mother tongue and requested to provide written informed consent prior to study enrollment. If consent is provided, a unique Study ID will be assigned. All included participants will be asked to provide a telephone number where they can be reached (personal or to a relative), for later contact tracing if needed. Participants can withdraw from the study at any given time.

### Eligibility criteria

All adults (>18 years of age) and who are HBsAg positive and provide informed consent are eligible for inclusion. Inclusion and exclusion criteria are given in Table 2.

**Table 2 Tab2:** Inclusion and exclusion criteria of the study

**Inclusion criteria**	**Exclusion criteria**
Adults (>18 years of age)	Below 18 years of age
HBsAg positive. Informed consent	Negative HBsAg rapid test at screening visit
	HIV positive
	Other disease with short life expectancy (advanced HCC, disseminated cancer, etc.)

*Abbreviations: **HbsAg* hepatitis B surface antigen, *HCC* hepatocellular carcinoma, *HIV* human immunodeficiency virus

### Liver disease assessment 

Liver disease assessment will be based upon ALT, aspartate aminotransferase to platelets ratio (APRI) score and clinical assessment (signs of decompensated liver disease) in the standard model, APRI and clinical assessment in the simplified model, and clinical assessment in the test-and-treat model. Laboratory tests at baseline and at follow-up depends on which model of care the study site is assigned to (Table 1). All models will consider radiological signs of liver disease if the participant has undergone imaging the previous 3 years before enrolment, but imaging will not be part of the routine assessment.

### Treatment initiation and follow-up

If a participant is eligible for treatment, pre-treatment counselling will be delivered by a member of the team. Participants will be encouraged to bring a familiy member or friend to the counselling to reduce stigma and promote adherence. Counseling will focus on the natural course of hepatitis B, its long-term consequences, benefits of therapy, possible side effects, the risk of resistance with irregular treatment, and the risk of hepatitis flares if treatment is interrupted. Patients will be warned against excessive alcohol and khat use, herbal medications and over-the-counter drugs. Sex partners and children will be encouraged to be tested, and those without evidence of current or past infection will be advised to get HBV vaccine.

Treatment consists of tenofovir disoproxil fumarate (TDF) 300mg tablets, taken once daily. All patients will be followed up for the duration of the trial, but at various intervals depending on model of care and treatment status (Table 1). Patients with signs of advanced chronic liver disease (ascites, jaundice, confusion, upper GI bleeding) at inclusion will start treatment immediately and get an appointment with a doctor within 2 weeks to evaluate if they need other supportive treatment and care.

At the follow-up appointments the local investigator / study nurse will communicate the previous laboratory results and reiterate what the study entails and pinpoint the responsibilities of the patient. Patients will be asked about adverse events and adherence to therapy. Full clinical examination is not required, but evidence of hepatic decompensation (ascites, jaundice, confusion, upper gastrointestinal bleeding) will be noted.

Patients who do not attend follow-up consultations will be contacted by the team. All participants will be provided with *patient appointment cards* that state their Study ID and the date of their next appointment. If possible, we will send an SMS or call to remind them about the appointment 1 week ahead of time.

Upon inclusion, drugs will be dispensed for 3 months. Once the patient proves to be adherent to therapy, drugs can be dispensed for 6 months by the study team. Empty pill boxes should be brought to each visit for pill count, and the study nurse will register the number of pills dispensed and returned for each follow-up appointment*.*

In individuals without liver cirrhosis, treatment can be stopped if there are two consecutive negative HBsAg RDTs minimum three months apart.

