## Methods

### Study design

This will be prospective cohort study comparing three models of decentralized care for the management of CHB in Ethiopia. The overreaching research question is “What is the best model of care for testing, treatment, and follow-up in a primary hospital/health center in rural Ethiopia”. The three models of care will be assessed both from a clinical, programmatic and implementation perspective.

Testing, screening and linkage to care is common for the three model, but the treatment protocol differs. The standard model utilizes the WHO 2024 treatment guideline for hepatitis B to identify individuals at *high risk* of disease progression («*treat only if.*.») [11]. As most primary hospitals in Ethiopia lack assess to HBV DNA testing, we will use the WHO treatment eligibility criteria for settings without an HBV DNA analysis option (Table 1). The simplified model will utilize clinical and laboratory criteria to identify patients at *low risk* of liver injury, who will be exempted from treatment («*treat all except …*»). Finally, the test-and-treat model will offer treatment to all individuals with CHB (“*treat all*”), mimicking the models of care that have been successfully assessed and implemented for HIV and hepatitis C [17]. This latter model avoids the complicated patient assessment and the demand for expensive laboratory tests.

**Table 1 Tab1:** The three models of care to be assessed in the study: treatment criteria, laboratory analyses required, and scheduled follow-up

	Standard model “treat only if…”	Simplified model “treat all except…”	Test and treat model “treat all”
Treatment criteria	Treat *only* if:	Treat all, *except* if:	Treat all
	-Clinically diagnosed cirrhosis	-There are no signs, symptoms or risk factors for liver disease, *AND*	
	-APRI above 0.5	-APRI is 0.3 or below	
	-Persistently elevated ALT		
	-Co-infections and co-morbidity		
	Pregnant women: treat to prevent mother-to-child transmission		
Laboratory analysis required at inclusion	AST, ALT, platelets, (Creatinine^1^)	AST, platelets (Creatinine^1^)	(Creatinine^1^)
	HIV, HCV, HBsAg RDTs	HIV, HCV, HBsAg RDTs	HIV, HCV, HBsAg RDTs
Follow-up:on treatment	Physical examination, HIV, and pharmacy refill at 3 months, then every 6 months	Physical examination, HIV, and pharmacy refill at 3 months, then every 6 months	Physical examination, HIV and pharmacy refill at 3 months, then every 6 months

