	AST, ALT, platelets, (creatinine^1^), HBsAg, DBS every 12 months	AST, platelets, (creatinine^1^), HBsAg, DBS every 12 months	(Creatinine^1^), HBsAg, DBS every 12 months
Follow-up:*not* on treatment	Physical examinationAST, ALT, plateletsHBsAg,DBSevery 6 months	Physical examinationAST, plateletsHBsAg,DBSevery 6 months	N/A

*Abbreviations**: ALT* alanine aminotransferase, *APRI* aspartate aminotransferase to platelets ration, *AST* aspartate aminotransferase, *HCV* hepatitis C virus, *HbsAg* hepatitis B surface antigen, *HIV* human immunodeficiency virus, *DBS* dried blood spot testing, *N/A* Not applicable, *RDT* rapid diagnostic test

^1^ Only required in patients at risk of renal disease, i.e. individuals with hypertension, diabetes, use of nephrotoxic drugs, or age above 60 years

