### Outcomes 

The primary endpoint will be either death or liver decompensation (composite endpoint). Liver decompensation will be detected clinically (ascites, jaundice, encephalopathy, upper gastrointestinal bleeding). Deaths will be verified by health extension workers, who will trace/identify patients WHO miss appointments for more than 3 months. Health extension workers are individuals with a minimum of 10^th^ grade schooling who are part of the Ethiopian public health extension program. Each village has two health extension workers whose main responsibility is to deliver preventative and promotive health services at community level.

Secondary endpoints include programmatic outcomes (linkage to care, retention in care) and laboratory outcomes (viral suppression *viz*HBV DNA ≤10 IU/ml; new HIV infection). HBV DNA is not part of routine care at these sites but will be collected using dried blood spots (DBS) during the study period and measured after completion of the observation period (three years) for those who have received treatment, using the Xpert HBV viral load kit (Cepheid, CA, USA). 

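### Table 1 schedules no follow-up for test-and-treat participants who are off treatment, so ascertainment of the primary endpoint is undefined for them in that model only

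*Protocol article*

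**What the plan says.** All places are in the Protocol article.

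- **Treatment initiation and follow-up** makes a promise that covers every participant: "All patients will be followed up for the duration of the trial, but at various intervals depending on model of care and treatment status". It cites Table 1 for the intervals.
- **Study design, Table 1**, in the row "Follow-up:*not* on treatment", gives an examination and laboratory visit every 6 months in the standard model and in the simplified model. The test-and-treat cell is N/A.
- **Study design** describes treatment in that model as an offer: "the test-and-treat model will offer treatment to all individuals with CHB".
- **Treatment initiation and follow-up** also sets a stopping route for people without cirrhosis, not limited to any model: "treatment can be stopped if there are two consecutive negative HBsAg RDTs minimum three months apart".
- The same section says what happens at follow-up appointments: "evidence of hepatic decompensation (ascites, jaundice, confusion, upper gastrointestinal bleeding) will be noted".
- **Outcomes** makes death or clinically detected decompensation the primary endpoint, and describes how deaths are found: "Deaths will be verified by health extension workers, who will trace/identify patients WHO miss appointments for more than 3 months".
- **Statistical analysis** right-censors people lost to follow-up at the date last known alive, and adds a worst-case analysis that counts missing outcomes as events.

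**The concern.** The text sends the reader to Table 1 for the interval that applies to a given model and treatment status. For one combination, test-and-treat and off treatment, Table 1 has no interval. N/A would be harmless if that group were empty by design, but the protocol leaves at least two ways into it: declining the offer while staying enrolled, and stopping under the HBsAg rule.

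Both parts of the primary endpoint lean on appointments. Decompensation signs are noted when the participant attends, and health extension workers start tracing when an appointment is more than 3 months overdue. Without a scheduled appointment, neither has a defined trigger. The other two models see their off-treatment participants every 6 months, so the gap is not shared. It falls on one side of the contrast that the sample size is built on, standard against test-and-treat. If contact lapses and these people are censored, the test-and-treat estimate moves towards an on-treatment estimate, while the comparators remain whole cohorts.

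**Working it through.** **1. Can the group exist?** Eligibility requires HBsAg positivity and consent to the study, with no requirement to accept tenofovir. A decliner can therefore be enrolled from day one. A stopper under the HBsAg rule comes later. Table 1 tests HBsAg every 12 months on treatment, and the second negative test must be at least 3 months after the first. On the scheduled tests plus one repeat, the earliest stop is about month 12 + 3 = 15 of 36.

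**2. Does another provision supply the visit?** Appointment cards go to all participants and non-attenders are contacted, but both presuppose a date for the next appointment. The place that should set that date is the N/A cell.

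**3. What would the planned analysis do?** Someone out of contact is censored at the date last known alive. Take w as the share off treatment, r_off and r_on as the 3-year risks, and r_S as the risk in the standard model. Approximate early censoring by removing the off-treatment group from the risk set:

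- true RR = [w × r_off + (1 − w) × r_on] / r_S
- observed RR = r_on / r_S

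r_S = 5% comes from the sample size section. The documents give neither w nor r_off, so both are assumptions.

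**4. No true difference (overall test-and-treat risk 5%), w = 20%**

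| r_off | r_on | Overall risk | Observed RR |
|---|---|---|---|
| 8% | 4.25% | 0.2 × 8% + 0.8 × 4.25% = 5.0% | 4.25/5 = 0.85 |
| 5% | 5% | 5.0% | 1.00 |
| 2% | 5.75% | 0.2 × 2% + 0.8 × 5.75% = 5.0% | 5.75/5 = 1.15 |

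The direction follows whether r_off is above, equal to or below r_on.

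**5. Planned effect among the treated.** The sample size section assumes 5% against a 50% relative reduction. A two-sided continuity-corrected calculation for 5% against 2.5% gives 984 per arm, 1.3% below the stated 997, so these inputs are the plan's own. With r_on = 2.5%, r_off = 5% and 1,500 in the arm:

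| w | Events in off-treatment group | All events | True RR | Observed RR if censored |
|---|---|---|---|---|
| 2% | 1.5 | 38.25 | 0.51 | 0.50 |
| 5% | 3.75 | 39.375 | 0.525 | 0.50 |
| 10% | 7.5 | 41.25 | 0.55 | 0.50 |
| 20% | 15 | 45 | 0.60 | 0.50 |

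If r_off is also 2.5%, the true RR is 0.50 and censoring changes nothing.

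**6. Does the worst-case analysis settle it?** With w = 20% missing and counted as events, the test-and-treat risk becomes 0.8 × 2.5% + 20% = 22%. The planned inflation already allows for attrition of 1 − 997/1,500 = 33.5%. At that level, imputed events swamp a contrast of 5% against 2.5%, so the analysis cannot isolate this gap.

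**The case against.** The strongest reply is that N/A simply means nobody is ineligible under a treat-all rule. On that view the general provisions apply to everyone: follow-up for the whole trial, an appointment card, and contact after non-attendance. No passage says that off-treatment test-and-treat participants leave follow-up. Someone who merely stops attending is still on the on-treatment schedule and is traced. The article also condenses a full protocol, which may hold the missing instruction.

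Much of this stands, and it limits the point. A reader might infer that these participants' events are lost. The documents do not show that; they leave ascertainment undefined for decliners and stoppers who remain enrolled. A reader might also compute that with 10% to 30% off treatment and none of their events seen, a true ratio of 1 would appear as 0.90 to 0.70. That requires them to stay in the risk set, event-free, to the end of follow-up, which conflicts with the planned right-censoring. Nor do the documents support a bias that always favours test-and-treat. The HBsAg stopping route selects people without cirrhosis and with repeated negative tests, who may be at lower risk than those who continue.

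The appeal to the condensed format does not remove the point. The article prints the visit schedule, and one cell of it conflicts with the article's own text. That is a contradiction, not an omitted detail.

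**Conclusion.** The point holds as an internal contradiction with a possible effect on the primary endpoint. Table 1 gives no follow-up for a group that the protocol itself allows, the text promises follow-up to all, and the other two models see the same kind of participant every 6 months. The consequence is a risk of differential ascertainment or informative censoring, not a demonstrated loss of events.

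Its size cannot be fixed from the documents. Under censoring, the observed ratio is about 0.85 in place of 1 with 20% off treatment at 8% risk and 4.25% on treatment. Both the share and the 8% are assumptions, and the calculation treats everyone affected as off treatment from enrolment, which fits decliners better than stoppers. At a 2% share, with 5% risk off treatment and 2.5% on it, the ratio moves only from 0.51 to 0.50. The bias favours test-and-treat if those off treatment are at higher risk than those on it, and is nil or reversed if their risk is equal or lower. The change is worth making because it is cheap and recruitment is described as ongoing, while contacts not made cannot be recovered.

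**What to change.** Reconcile Table 1, the two follow-up and stopping statements under Treatment initiation and follow-up, and the tracing rule under Outcomes:

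- Replace N/A with a scheduled outcome contact for every enrolled test-and-treat participant who is off treatment, for whatever reason. It should record vital status and the four decompensation signs, and be comparable with what off-treatment participants receive in the other models.
- State that a missed contact triggers the existing tracing by health extension workers.
- State that decliners and stoppers stay in their site's model in the primary analysis.

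This concerns outcome collection only. It prescribes no treatment, laboratory or stopping rule. The cost is one table entry, an instruction for the case report form, and a small number of extra contacts by existing staff at the two test-and-treat sites.

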### Pregnant women

Pregnant women will be offered antiviral treatment for their own health if they fulfil the criteria in the designated model. In any case, pregnant women will be given antiviral treatment from gestational week 24-28 to prevent mother-to-child transmission of HBV. This is in addition to recommending three-dose hepatitis B vaccination in all infants, plus timely (within 24 hours) birth dose vaccine. If the mother does not fulfil any of the treatment criteria (individual, for own health), treatment can be stopped once the infant has completed the HBV vaccination series (usually given at 6-10-14 weeks of age). 

All mothers enrolled in the program must be asked to return with their baby at the age 6-12 months for a HBsAg rapid test.

### Management of HCC 

Participants with an abdominal mass suspect of HCC, either at inclusion or at follow-up, will be referred to further diagnostic and therapeutic procedures based on local availability.

### Data collection and management 

Data will be collected prospectively during the study period and entered into an electronic case report form (RedCap) by data clerks at the various sites. Data quaility will be monitored monthly by a central data manager, and missing data/queries will be communicated to the teams on regular intervals. Names, date of birth, contact information and health information are collected from participants. Forms containing participant information will be kept at locked and secure locations at the study sites. Data will be entered in RedCap using study-specific ID numbers, but names, date of birth or other identifiable information will not be entered. No code-list will be used. To ensure confidentiality, only data clerks and members of the project managemnt group has access to the RedCap data set. Only members of the project management group will have access to the final data set.

